## Automated Classifier Construction

Training, testing, and cross-validation of automated classifiers will follow methods previously described for disease state classification using support vector machines (SVM). First, for each feature within the a given map, the Kendall tau rank correlation coefficient will be calculated as a non-parametric measure of the feature's relevance in discriminating responders from nonresponders. Next, features will be ranked according to discriminative power (i.e., absolute value of tau). Next, a leave-one-out cross validation approach will be used, omitting one subject per iteration during classifier training. Next, the set of consensus features (showing significant discriminative power across all 200 iterations) will be identified. This set of features will be used for construction and performance evaluation of the SVM. Classifier performance will be evaluated both in terms of overall accuracy and negative predictive value. The probability of obtaining the calculated performance under the null hypothesis will be determined using permutation testing, in which the class labels of the training data are randomly permuted and the training and cross-validation repeated, over 10 000 iterations, as previously described. SVM performance in discriminating responders from non-responders will be assessed by this method on each of the 4 feature sets described above. The performance of each classifier will be compared using the area-under-the-curve of the receiver-operating characteristic, chi-squared tests on overall accuracy and negative predictive value, and the decision-analytical approach of Vickers, which accommodates a spectrum of thresholds for pursuing or foregoing treatment.

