#### 1.4.0 Objectives and Hypotheses

In summary, TBS has been shown to be effective in open-label studies of major depression. It has also been shown to have greater potency than conventional protocols in studies of motor physiology. However, to date there has been no direct comparison of the relative efficacy of these different forms of rTMS for TRLLD under randomized controlled conditions. This study will address the question of the relative efficacy of conventional versus theta-burst stimulation in the setting of TRLLD by comparing conventional HFL rTMS to TBS, while training and validating classifier algorithms for predicting treatment response using rs-fMRI.

[figure not shown]

**Objective 1:** To compare the effectiveness of a course of 4 minute sessions of TBS to a course of 45 minute sessions of conventional rTMS in LLD.

**Hypothesis 1:** Sequential bilateral forms of TBS will have non-inferior effectiveness compared to sequential bilateral conventional rTMS in older adults with depression.

**Objective 2:** To determine if an automated classifier can use pre-treatment resting-state fMRI, clinical and cognitive data to predict treatment outcome for both TBS and conventional rTMS.

**Hypothesis 2:** Patterns from whole-brain functional connectivity, obtained from pre-treatment rs-fMRI, will distinguish responders and nonresponders with >85% accuracy for TBS and standard rTMS.

**Exploratory Objective 1:** To compare network connectivity in depressed adults across the lifespan and rTMS-induced changes between bilateral and unilateral stimulation approaches using existing unilateral data in adults <60 from our group.

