### 3.2.3 Outcome Analysis

**Objective#1:** Assessing non-inferiority of bilateral TBS based on change on the MADRS, an ANCOVA covarying for baseline differences will be used to measure the change at the final time point for each subject. This will be the primary clinical outcome measure.

Secondary outcome measures will include change from baseline to endpoint on the HDRS-17 and response and remission on the HDRS-17 and MADRS.

For categorical outcome measures, response will be defined as  $\geq 50\%$  reduction in symptoms on the HDRS-17. Remission will be defined as a HDRS-17  $\leq 10$  and a MADRS  $\leq 10$  at the week 4 or 6 final time point. Other secondary outcome measures will explore comparison of side effects between the two treatment arms, anxiety scales, quality of life scales and cognitive measures.

**Objective#2:** Outcome prediction from whole-brain rs-fMRI scans, data will be analysed using the FSL platform and in-house scripts to extract whole-brain regional connectivity matrices, followed by automated classifier training, using a support vector machine approach according to previously reported methodology. Based on preliminary data, classifiers will be trained on 4 features: whole-brain functional connectivity, region-wise betweenness centrality, and edge-wise functional connectivity variability. Automated classifiers will be trained and tested on the datasets for standard bilateral groups, with iterative cross-validation to ensure generalizability.

[figure not shown]

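### The classifier's consensus features are chosen with every subject's outcome and then scored on those same subjects, so accuracy, NPV and AUC for Objective 2 are biased upward

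*Protocol*

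**What the plan says.** Hypothesis 2 (Protocol 1.4.0) is that connectivity patterns "will distinguish responders and nonresponders with >85% accuracy for TBS and standard rTMS".

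The section Automated Classifier Construction sets out an ordered procedure:

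1. For every feature, "the Kendall tau rank correlation coefficient will be calculated as a non-parametric measure of the feature's relevance in discriminating responders from nonresponders". Features are then ranked by the absolute value of tau.
2. After that, "a leave-one-out cross validation approach will be used, omitting one subject per iteration during classifier training".
3. Then "the set of consensus features (showing significant discriminative power across all 200 iterations) will be identified".
4. Then "This set of features will be used for construction and performance evaluation of the SVM".
5. For the p-value, "the class labels of the training data are randomly permuted and the training and cross-validation repeated, over 10 000 iterations".

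Accuracy, negative predictive value and AUC are computed for each of four feature maps. Section 3.2.3 (Outcome Analysis) relies on training and testing "with iterative cross-validation to ensure generalizability". No hold-out or replication sample is described, although the background (1.3.0) faults earlier classifier studies for not testing on a second dataset.

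**The concern.** Cross-validation estimates performance in new patients only if the held-out subject played no part in building the model, and choosing features by their association with outcome is part of building it. Here a single feature set is distilled from all iterations and then used both to build and to score the classifier. The leak exists on either reading of the first step. If tau is computed once on all subjects, it is direct. If tau is recomputed in each iteration, intersecting the results over all iterations brings the held-out labels back in.

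Objective 2 is one of the protocol's two numbered objectives, and section 2.0 foresees a pre-treatment scan that would steer likely non-responders away from treatment. An inflated accuracy or negative predictive value would bear directly on that use.

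**Working it through.** **Inputs from the protocol.** 200 subjects, 100 per arm (3.2.1); 200 iterations and 10,000 permutations (Automated Classifier Construction); 516 regions (neuroimaging section of 3.2.3); threshold >85% (1.4.0). Response rate 50%, the lower end of the 50–55% in 1.1.2.

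**Assumptions, because the protocol gives no figure.** Selection level (p<0.05, with p<0.01 as the stricter case), SVM cost setting, correlation among features.

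**The plan's own figure.** The 200 iterations match the sample size: n per arm = 2 × (1.645 + 0.842)² × 7.8² / 2.75² = 2 × 6.18 × 8.045 ≈ 99.5, so 100 per arm (one-sided 0.05), as stated. The >85% has no calculation behind it to reproduce.

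**Extent of the leak.** Each subject is in the training data of 199 of 200 iterations. Any two training sets share 198 of their 199 subjects, so significance in all of them is not replication. The connectivity and connectivity-variability maps each hold 516 × 515 / 2 = 132,870 edges. On noise at p<0.05, about 132,870 × 0.05 ≈ 6,640 would pass in one dataset; in simulation about 5,090 passed in all 200 iterations.

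**Null simulation of the written sequence.** Features were pure noise; those significant in every fold were kept, and a linear SVM on that fixed set was scored by leave-one-out. Entries are mean accuracy with range, over 3 to 20 runs per setting except the last row, which shows two single runs.

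| Noise features | Level | n=200 | n=100 |
|---|---|---|---|
| 516, independent | 0.05 | 72.2% (65.5–78.5) | 76.7% (65–91) |
| 516, independent | 0.01 | 63.8% (57.5–70.5) | 67.9% (58–75) |
| 10,000, independent | 0.05 | 99.3% (98.5–100) | 100% |
| 10,000, independent | 0.01 | 89.7% (83.5–96.5) | 97.8% (95–99) |
| 132,870, independent | 0.05 and 0.01 | 100% | 100% |
| 132,870, correlated | 0.05 | 85.3% (84–87) | 92.7% (92–93) |
| 132,870, correlated | 0.01 | 85.0% (84.5–86) | 90.0% (87–92) |
| 132,870, correlated, second SVM setting | 0.05 | 79%, 84.5% | 88%, 90% |

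The correlated features have 50 shared factors carrying half the variance. A separate simulation with a regularised least-squares classifier gave 71% (n=200) and 79% (n=100) on 516 features, and 96.5% on 132,870 independent features at p<0.001, n=200. Another gave 79–84% (n=200) and 85–89% (n=100) with correlated features.

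With 35% responders, independent edges still gave 100%. Correlated edges gave 82–86% (n=200) and 94–96% (n=100), but only 58–73% under an SVM setting that in effect suppressed the intercept.

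**Selection redone inside each fold** (10,000 noise features, four runs each): 35.5%, 40%, 50.5%, 62.5% at n=200 (mean 47%); 35%, 67%, 35%, 46% at n=100 (mean 46%). This is chance level. It was not run at 132,870 features.

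**Permutation test** (10,000 noise features, n=200, observed accuracy 98.5%, 40 permutations):
- Feature set held fixed: permuted accuracy averaged 50%, maximum 62.5%. None reached the observed value, so p = 1/41 ≈ 0.024, the smallest attainable.
- Selection repeated: permuted accuracy averaged 99.4%, minimum 98.5%. All 40 reached the observed value, so p = 41/41 = 1. The test exposes the noise, but the reported 98.5% does not change.

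**The case against.** The strongest objection concerns the permutation test. The section introduces ranking and selection under the general label of training, testing and cross-validation, so the training that is repeated in each permutation can fairly be read to include selection. On that reading the p-value is protected, and a high accuracy with a non-significant p would not plainly be reported as success. This stands. A reader might infer that the p-value is invalid as written, or that a worthless classifier would be declared to confirm Hypothesis 2. The text supports neither; it does not say whether selection is repeated.

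The size is also open to challenge. Edges derived from 516 regional time-courses are unlikely to be independent, so 100% is a worst case, and the assumed correlation brings n=200 results to around the 85% line. A reader might infer that noise would pass 85% on every map. On 516 features it did so only occasionally, at n=100, and the voxelwise map was not simulated because its size is not stated.

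Finally, the protocol refers to previously published methods, and an analysis plan may add detail. Either could settle the selection level and the scope of the permutations. Neither removes the explicit statement that the consensus set is used for performance evaluation.

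**Conclusion.** The point holds for the performance estimates: accuracy, negative predictive value and AUC for Objective 2 are biased upward as the procedure is written.

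With no signal and 50% responders, apparent accuracy on a map of betweenness size is roughly 70–80% at p<0.05 and 64–68% at p<0.01. On edge-based maps at n=200 it is roughly 79–87% with correlated features and 90–100% with independent ones (the lower end from 10,000 features at p<0.01). The bias is larger if classifiers are trained per arm, with about 100 subjects each. Noise can therefore reach the >85% of Hypothesis 2 on the high-dimensional maps, but not reliably on the betweenness map.

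The direction of the bias follows from the text; its size depends on the unstated selection level, the SVM setting, the correlation among features and n, and rests on few runs per setting. The p-value is invalid only if selection is not repeated in the permutations. The non-inferiority comparison on the MADRS does not use the classifier and is unaffected.

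**What to change.** Rewrite the sequence in Automated Classifier Construction as follows:

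- Redo the Kendall-tau ranking, the significance filter and any SVM tuning inside each training fold, without the held-out subject.
- Take accuracy, negative predictive value and AUC only from those held-out predictions.
- Report the features selected in all iterations as description only, not as the set on which performance is evaluated.
- State that each of the 10,000 permutations permutes the labels once for the whole dataset and reruns the full pipeline, including feature selection.

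No new data are needed. The cost is wording, computing time (10,000 × 200 = 2,000,000 fold-level selections per map) and a lower reported accuracy. The change can be made at any time before the classifier analysis is run.

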## 3.3 Regulatory Compliance and Monitoring

### 3.3.1 ClinicalTrials.gov Registration

This study will be registered on [www.clinicaltrials.gov](http://www.clinicaltrials.gov) as is required by the FDA and regulatory authorities.

**Table 1. Schedule of Events**

| Clinical and Cognitive Assessments* | Screening and Baseline | Acute Phase:
Daily TBS or HFL rTMS             |                                     | Follow-up Assessments                           |                                            |
|-------------------------------------|------------------------|---------------------------------------------------|-------------------------------------|-------------------------------------------------|--------------------------------------------|
|                                     | Week 0                 | Weeks 1–3 (4&5 if responder) after every 5 visits | Final Visit: Week 4 or 6 or Dropout | 1 and 4 weeks following final treatment session | 12 weeks following final treatment session |
| MINI                                | X                      |                                                   |                                     |                                                 |                                            |
| TASS                                | X                      |                                                   |                                     |                                                 |                                            |
| SBT                                 | X                      |                                                   |                                     |                                                 |                                            |
| MoCA                                | X                      |                                                   | X                                   |                                                 | X                                          |
| BSI-Anxiety                         | X                      |                                                   | X                                   |                                                 | X                                          |
| ATHF                                | X                      |                                                   |                                     |                                                 |                                            |
| BSS                                 | X                      | X                                                 | X                                   | X                                               | X                                          |
| HRSD-17                             | X                      |                                                   | X                                   | X                                               | X                                          |

[figure not shown]

|                                |   |   |   |   |   |
|--------------------------------|---|---|---|---|---|
| MADRS                          | X | X | X | X | X |
| QIDS-16                        | X | X | X | X | X |
| Q-LES-Q                        | X |   | X |   | X |
| CIRS-G                         | X |   |   |   |   |
| Side effect report             | X | X | X |   |   |
| D-KEFS Color-Word Interference | X |   | X |   | X |
| Test of Premorbid Function     | X |   |   |   |   |
| CVLT-II                        | X |   | X |   | X |
| NIH Toolbox Flanker Test       | X |   | X |   | X |
| MRI                            | X |   | X |   |   |

ATHF: Antidepressant Treatment History Form

BSI-anxiety: Brief Symptom Inventory-anxiety subscale

BSS: Beck Suicide Scale for Suicide Ideation

CIRS-G: Cumulative Illness Rating Scale for Geriatrics

CVLT-II: California Verbal Learning Test – Second Edition

HRSD-17: 17 Item Hamilton Rating Scale for Depression

MADRS: Montgomery Asberg Depression Rating Scale

MoCA: Montreal Cognitive Assessment

MINI: Mini International Neuropsychiatric Interview

QIDS-16: 16-item Quick Inventory of Depressive Symptoms

Q-LES-Q: Quality of Life Enjoyment and Satisfaction Scale

SBT: The Short Blessed Test

TASS: Transcranial Magnetic Stimulation Adult Safety Screen.

\*see proposal text for description and rationale

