Depressive symptoms will be assessed using the clinician-rated Montgomery Asberg Depression Rating Scale (MADRS), the 17-Item Hamilton Depression Rating Scale (HRSD-17), and the self-rated 16-item Quick Inventory of Depressive Symptoms (QIDS16). Change in scores on the MADRS, from baseline to endpoint, will be the primary clinical outcome of interest. The primary neuroimaging outcome measure will be the whole-brain functional connectivity on rs-fMRI. If the subject experiences an improvement in their symptoms by a minimum of 30% based on the change in MADRS score from baseline to week 4, they will receive an additional 10 treatments over the course of 2 weeks in an attempt to optimize treatment response. Those subjects that do not achieve a 30% reduction by week 4 will be given the opportunity to continue for 2 more weeks as they may be late responders and benefit from the additional 10 treatments. All participants will undergo a post-treatment MRI scan after they complete treatment. Participants who are in remission at weeks 3 and 4 will exit the study at week 4 and undergo a post-treatment MRI scan. For participants who do not wish to continue past week 4 they will undergo a post-treatment MRI scan (30 minutes) and complete all final visit measures.

An independent, trained rater at each site will administer the clinical assessment scales at baseline, after each 5 sessions of treatment, and at 1, 4, and 12 weeks post-treatment. Cognitive assessments will be administered at baseline, after the final treatment session (including at drop-out), and at 12 weeks following the final treatment. These assessments can be done within 1-2 days of the scheduled time point. The independent raters will be blinded to the treatment being administered. All treatments will be conducted with minimization of personal contact (i.e., verbal communication) with the subject to reduce the impact of nonspecific therapeutic contact on outcomes. Patients who participate in the study will not be allowed to meet with each other before, during and after assessment or treatments in order to maintain the blind. Patients will be discontinued if they experience worsening in depression, where worsening of depression is defined as an increase in MADRS from baseline of more than 25% during two consecutive assessments, or development of active suicidal intent or attempted suicide.

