#### Clinical Assessments During and After Treatment:

Clinical outcome measures will be assessed in the week prior to treatment, after each 5 sessions of treatment, then at 1, 4, and 12 weeks after treatment. These assessments can be completed over the phone if the participant is unable to attend the visit within the given time frame. The MADRS will be the primary

[figure not shown]

outcome measure and a score of greater than or equal to 18 will be used to establish eligibility. The HDRS-17 is the most commonly used outcome measure in previous randomized trials of rTMS and will be included for comparison purposes. However, the MADRS is well validated in LLD and has been used in trials of other interventions in TRLLD and will therefore be the primary measure. Secondary outcome measures will include the HDRS-17 and the self-rated QIDS16. The BSS will be administered after each 5 sessions of treatment, then at 1, 4, and 12 weeks post treatment as a safety measure to assess for suicidality.

To assess other potential predictors of response of rTMS we will assess anxiety, quality of life and medical burden. We will use the Brief Symptom Inventory – Anxiety, the Quality of Life Enjoyment and Satisfaction Scale (Q-LES-Q), and the Cumulative Illness Rating Scale for Geriatrics (CIRS-G).

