Common side effects of rTMS treatment are headache, discomfort and or pain at the stimulation site, facial muscle twitching, neck discomfort or pain, light-headedness or dizziness. These symptoms are expected and will be recorded separately from adverse events as side effects.

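### Table 1 limits the week 4 and 5 interim assessments to responders, although participants below 30% improvement may also continue to week 6; only the side-effect report is left without other timing (minor)

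*Protocol*

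**What the plan says.** **Table 1 (Schedule of Events).** The acute-phase interim column is headed "Weeks 1–3 (4&5 if responder) after every 5 visits". The column after it is headed "Final Visit: Week 4 or 6 or Dropout". The interim column is marked for the BSS, MADRS, QIDS-16 and side-effect report. It is not marked for the HRSD-17.

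**Section 3.1.1, who continues.** Participants with at least 30% MADRS improvement at week 4 receive 10 more sessions over two weeks. The others are not stopped: "Those subjects that do not achieve a 30% reduction by week 4 will be given the opportunity to continue for 2 more weeks". One group leaves early: "Participants who are in remission at weeks 3 and 4 will exit the study at week 4".

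**Section 3.1.1, rating frequency.** The independent rater "will administer the clinical assessment scales at baseline, after each 5 sessions of treatment", and again during follow-up.

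**Section 3.1.5 (Clinical Assessments During and After Treatment).** The same five-session interval is given for the outcome measures, and separately for suicidality: "The BSS will be administered after each 5 sessions of treatment".

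**Section 3.1.1, stopping for worsening.** A participant is discontinued after "an increase in MADRS from baseline of more than 25% during two consecutive assessments". Active suicidal intent or an attempt is a separate ground for stopping.

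**Section 3.1.6, side effects.** Expected symptoms "will be recorded separately from adverse events as side effects". No timing is given. Section 3.2.3 lists the comparison of side effects between arms among the other secondary outcomes.

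**The concern.** The header fits a design in which only improvers are extended. Section 3.1.1 extends two groups, so the schedule and the text disagree about what is collected from a participant below 30% who accepts the extra sessions.

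For the depression scales and the BSS, the text supplies the missing instruction. For the side-effect report it does not: Table 1 is the only place that says when the report is taken. As written, its collection after week 3 depends on how well the participant is doing, and those doing less well are asked less often over the same 30 sessions. That is an undesirable feature in a tolerability measure that the protocol intends to compare between arms.

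A second, conditional consequence concerns safety. If site staff worked from the table alone, continuing non-improvers would have no BSS at week 5, and the two-assessment worsening rule would have no rating on which to act during the extension.

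**Working it through.** The protocol states no figure on this point, so there is none to reproduce. The check is a comparison of the texts and a count of sessions.

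**Inputs.** Five sessions per week and 20 to 30 sessions in total (Section 3.1.1); ratings every 5 sessions (Sections 3.1.1 and 3.1.5); the Table 1 headers and marked rows. Week 4 is session 20 and week 6 is session 30.

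**Step 1: can a reading of *responder* rescue the header?**
- As shorthand for the 30% MADRS rule, it leaves out those below 30% who continue.
- As the protocol's only stated definition of response (at least a 50% reduction on the HDRS-17, Section 3.2.3), it leaves out those same participants unless they happen to meet it, and also anyone who passes the 30% MADRS rule without meeting it. The HRSD-17 is not scheduled in the interim column, so that status could not be read from it.
- Neither reading covers everyone who continues.

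**Step 2: scheduled points for a participant below 30% who completes 30 sessions.**

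| Source | Sessions | Count |
|---|---|---|
| Text (scales, BSS) | 5, 10, 15, 20, 25, 30 | 30 / 5 = 6 |
| Table 1, literal | 5, 10, 15, 30 | 4 |
| Table 1, with week 4 taken as the decision visit | 5, 10, 15, 20, 30 | 5 |

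For the MADRS the literal count of 4 is not realistic. The 30% decision and the remission exit both need a week-4 score from everyone.

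**Step 3: longest gap between side-effect reports, where only Table 1 applies.**
- Responder: 5 sessions.
- Continuing non-improver, literal header: 30 − 15 = 15 sessions (3 weeks at 5 per week).
- Continuing non-improver, if a report is also taken at the week-4 decision visit: 30 − 20 = 10 sessions (2 weeks). This depends on an added assumption, because the week-4 decision needs depression ratings and not a side-effect form.

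**Step 4: the worsening rule, if staff followed the table over the text.**
- A participant above baseline at week 4 has by definition not improved by 30%, so anyone whose worsening is first seen at session 20 and who continues is in the group at issue.
- Under the text, session 25 can confirm it, with 30 − 25 = 5 sessions left. Under the table, the next rating is the final visit at session 30, with none left.
- Worsening at sessions 15 and 20 is caught either way, because the week-4 MADRS is taken regardless.
- Worsening first seen at session 25 cannot be confirmed before session 30 even under the text.
- The table therefore changes one case only: worsening first seen at week 4.

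**The case against.** The strongest reply is that this is a leftover phrase in a column header. The text requires the scales and the BSS every five sessions without condition, the header itself repeats the five-visit interval, and the table's starred footnote sends the reader to the body text. This stands for the MADRS, QIDS and BSS: the protocol as a whole requires them at sessions 20 and 25. It does not help the side-effect report, for which the text gives no timing. Nor does the footnote say that the text prevails over the table on timing.

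It can also be said that little is lost: one or two forms per affected participant, with reports still taken at weeks 1 to 3 and at the final visit or dropout. That is fair, and it is why the point is minor.

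A reader might infer more in three ways, none of which the document supports:
- *A gap in suicidality monitoring or in the stopping rule.* The text requires these ratings. The loss arises only if staff follow the table instead, and the separate stop for suicidal intent or attempt applies throughout.
- *Bias between arms in the side-effect comparison.* The header applies to both arms alike. A difference would need unequal numbers of continuing non-improvers, and the protocol gives no basis for that.
- *An effect on the primary result.* The ANCOVA uses each participant's final time point, and Table 1 schedules a final visit at week 4, week 6 or dropout for everyone.

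**Conclusion.** Minor, but wrong as written. The Table 1 header contradicts Section 3.1.1 on who continues and Sections 3.1.1 and 3.1.5 on how often they are rated, and neither available meaning of *responder* reconciles them.

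The one consequence that needs no further assumption about conduct is that the side-effect schedule depends on response. Its size is the 15-session gap on the literal reading, falling to 10 if week 4 is also covered. The skipped week-5 BSS and the 5-session delay in confirming worsening are conditional on staff following the table over the text.

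The counts assume a participant below 30% at week 4 who accepts the extension and completes all 30 sessions. How many will do so cannot be derived from the protocol.

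**What to change.** Change the interim header to *Weeks 1–3 (and 4 and 5 for all who continue past week 4), after every 5 sessions*, and delete the responder condition. Participants who leave at week 4 stay under the final-visit column, so week 4 is not scheduled twice.

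This is a one-line edit. The text already requires the scales and the BSS at these points. The added work is two side-effect reports per continuing non-improver on the literal reading, or one if a report is already taken at the week-4 decision visit.
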